**Gait exercises**		
1. **Standing march with ARC device**	1 min	• Increase time • Increase the cueing frequency by 5% • Reduce the cueing frequency by 5% to work on control
2. **Walking and turning with ARC device**	10 short walks	• Increase time • Increase the cueing frequency by 5% • Reduce the cueing frequency by 5% to work on control • Walking and turning • Walking backwards • Walking whilst carrying an object, e.g. cup
3. **Manoeuvring between objects with ARC device**	Repeat each circuit 5 times (e.g. manoeuvring between two chairs and returning to start position)	• Increase number of circuits • Increase the cueing frequency by 5% • Reduce the cueing frequency by 5% to work on control • Change the objects to make them more difficult to manoeuvre around
4. **Basic community walking with ARC device**	5 min	• Increase time/distance walked • Increase the cueing frequency • Up and down curbs
5. **Advanced community walking with ARC device**	5 min	• Walking in busy areas, e.g. shopping mall • Walking on different surfaces, e.g. grass/sand • Up and down hills

One session of the ARC treatment per week will be supervised by the treatment provider, and during this session, ARC exercises will be progressed and new exercises added dependent on the needs of the participant. During the final 3 weeks of the treatment programme, supervised sessions will focus on ARC training in community settings. A menu of verbal cues will be given to the provider supervising the programme to ensure consistency of cues. To increase motivation, once participants have mastered stepping in time to the beat and are confident with the exercises, they will have the option of using music set at the same cueing frequency during their training sessions. Participants who opt to exercise to a music beat rather than the metronome will be provided with a track list of pieces of music with the correct beat and will be allowed to self-select their own music.

#### Mode of delivery

The ARC intervention treatment will be delivered by two providers (a research physiotherapist and a research associate). The treatment providers will supervise six of the ARC treatment sessions over the 6 weeks. The other 12 ARC treatment sessions will be undertaken independently by participants with telephone support from the treatment providers as necessary (maximum 6 telephone calls). All exercises will initially be supervised in order to determine whether participants are safe to undertake the exercises independently. All community walking sessions with the ARC device will be supervised to ensure safety.

### Study control treatment: gait and balance exercises

#### Dose and duration

Control participants will undertake a matched dose of balance and gait exercise treatment sessions to the intervention treatment group, e.g. three × 30-min sessions per week for 6 weeks (total 18 sessions).

#### Materials

Participants will be provided with paper- and web-based password-protected video-based training manuals on the control treatment programme. Participants will also be given an exercise diary to report adherence and a falls diary.

#### Procedures

Control participants will undertake the same exercises and progressions as the ARC intervention treatment group but without the ARC device and progressions specific to the ARC treatment programme, e.g. increasing the cueing frequency. Participants will be given basic instructions on the exercises but no cues of an auditory nature, e.g. any verbal timing cues whilst they undertake the exercises.

#### Mode of delivery

The control treatment will be delivered by two providers (a research physiotherapist and a research associate). In order to attention match, the control group will be contacted either face to face or by telephone once a week depending on the needs of the participant to check on the treatment progression. The other 12 control treatment group sessions will be undertaken independently with telephone support as necessary (maximum six phone calls over the 6-week period).

### Baseline assessment

A baseline assessment will be performed by a member of the study team following consent to study participation.

To characterise the cohort and inform treatment development, the following data will be collected:

*Demographic information*: Age, sex, pre-morbid function (Modified Rankin Scale) [27] pre-morbid walking status (with/without stick).

*Stroke information*: Date of stroke; stroke type (Ischaemic/haemorrhage); stroke classification subtype (TACS, PACS, LACS, POCS) [28].

The following measures will be taken at study baseline:

*Stroke-related characteristics*: Stroke impairment (National Institute of Health Stroke Scale) [29]; disability (Modified Rankin Scale) [27]; cognition (Montreal Cognitive Assessment) [30]; depression (Physical Health Questionnaire-9) [31]; fatigue (Fatigue Assessment Scale) [32]; walking aid use (with/without stick), ankle foot orthosis (yes/no, type).

*Gait, balance and health outcome measures*: Ambulatory ability (Functional Ambulation Category [33] and Rivermead Mobility Assessment) [34] spatiotemporal gait characteristics including gait speed, asymmetry and variability (4 metre walk test (× 5) recorded both manually and objectively with an AX3 accelerometer (see full description of AX3 below); postural control (2-min standing test objectively measured with an AX3 accelerometer) [35]; balance and gait (Mini Balance Evaluation Systems Test [36] and Activities-Specific Balance Confidence Scale) [37]; participation (Stroke Impact Scale) [38]; health outcome (EQ-5D-3 L) [39].

#### Seven-day measurement of gait and physical activity

At the baseline assessment, participants will be provided with an AX3 accelerometer to wear for 7 days before starting either the control or intervention treatment. The accelerometer will be collected by the treatment provider at the first session. Data on spatiotemporal gait characteristics and broader volume, pattern and variability of walking activity will be quantified using methods previously described [35].

#### Accelerometer description

The AX3 is a single tri-axial accelerometer-based wearable (AX3, Axivity, York, UK, https://axivity.com/, dimensions 23.0 mm × 3.25 mm × 7.6 mm). The AX3 weighs 11 g, has a memory of 512 Mb and a battery life of 14 days. AX3 data capture is 100 Hz (16-bit resolution) at a range of ± 8 g. Recorded AX3 accelerations store locally on the device’s internal memory and then downloaded upon the completion of each walking trial. The feasibility, validity and reliability of the AX3 accelerometer has been previously demonstrated for measuring spatio-temporal aspects of gait and physical activity in a stroke population in the clinic and the community [35].

### Randomisation

Sealed envelope centralised computer-based randomisation service (https://www.sealedenvelope.com/) will be used for randomisation. Allocation concealment will be ensured, as the randomisation code will not be allocated until after the participant has been consented into the trial. Randomisation will take place after all baseline outcome measures have been completed. Once baseline assessments have been completed by the assessors, the providers of the study treatments will use the sealed envelope randomisation service to randomise participants 1:1 into either the ARC intervention or control treatments. Simple randomisations will be used. The randomisation service will be used to number participants.

### Outcome assessments—6-week

The following outcomes will be gathered at the end of the 6-week treatment period.

#### Gait, balance, physical activity and health outcome measures

Gait and balance measures collected at baseline will be repeated (see the “Baseline assessment” section).

#### Seven-day measurement of gait and physical activity

On completion of the treatments, participants will be provided with an accelerometer to wear for 7 days. Participants will be asked to send the accelerometer back to the research team after the 7 days in a pre-paid envelope.

### Outcome assessments—10-week

#### Gait, balance and health outcome measures

Gait, balance and health outcome measures collected at baseline and 6 weeks will be repeated, in order to assess retention of post-treatment effects.

### Seven-day measurement of gait and physical activity

On completion of this assessment, the participants will be provided with an accelerometer to wear for 7 days. Participants will be asked to send the accelerometer back to the research team after the 7 days in a pre-paid envelope.

### Participant and provider views of the intervention

#### Participant views of the treatments

A questionnaire with a combination of closed and open questions will be provided to each of the participants developed with guidance taken from a previous feasibility study of physical activity after stroke via self-management [40].The questionnaires will either be collected by the study providers or returned in pre-paid envelopes.

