### Study objectives

Primary objectives:
To identify monthly recruitment rates to determine whether it is possible to enrol at least one patient per month from each study centre.To report participant adherence to ARC intervention and control treatment arms (provider observation and exercise diaries).To assess the acceptability and completeness of proposed methods of data collection to ensure they are feasible for a definitive trial.

Secondary objectives:
4.To report participant retention to the study.5.To report the success of outcome assessor blinding to participant treatment allocation.6.To report adverse events in control and intervention treatments during the study.7.To report the views of study participants about undertaking the ARC intervention at home and in the community.8.To report the views of providers and clinical therapists about the study protocol.9.To gather data to allow reporting of summary statistics to allow estimation of the sample size requirements for the definitive trial.

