### Progression criteria

Progression criteria have been set based upon recruitment, treatment adherence and data completeness to determine whether progression to a definitive trial is appropriate. These criteria and the traffic light system applied are based upon recommendations from Avery et al. [20].

Potential success criteria:
*Recruitment of participants*: green = an average of at least four patients per month recruited across the four sites; amber = an average of at least three patients per month recruited across the four sites; red = two or fewer patients recruited per month across the four sites.*Treatment adherence*: green = an average of at least 80% (840 out of 1080) supervised and self-monitored treatment sessions completed across the intervention and control treatment cohorts measured by provider observation and exercise diaries; amber = an average of at least 70% (756 out of 1080) supervised and self-monitored treatment sessions completed by participants; red = an average of 70% or less supervised and self-monitored treatment sessions completed by participants.*Data completeness:* green = completion (no missing data) of over 85% of key outcome measures (7 day accelerometer measurement; walking speed in the home; miniBEST and self-completion questionnaires: for full description see the ’Baseline assessment’ section) at 10-week outcome assessment for all those completing the treatment programmes; amber = completion of over 70% of key outcome measures at 10 weeks; red = completion of 70% or less of key outcome measures at 10 weeks.

Whilst these criteria will be used to evaluate the likely feasibility of a larger trial, they will primarily be employed to optimise the study design and identify/address issues in order to take remedial steps in a timely fashion. An example of this would be problems around recruitment.

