#### Providers’ views of the treatments

The therapist/researcher who has provided both the treatments will complete a questionnaire with a combination of closed and open questions specifically designed for this study in order to ascertain the feasibility of the treatments.

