### Data analysis

Objectives 1–3: Recruitment will be described as rate/month (total and per site). Adherence will be described using data from the exercise diaries (number of planned sessions completed). Acceptability and completeness of methods of data collection will be described using percentages from both treatments.

Objective 4: Retention will be described as percentage from both treatments.

Objective 5: The success of outcome measurement blinding will be described (%).

Objective 6: Adverse events pertaining to the study for each treatment will be described (number of events).

Objective 7: The views of study participants about undertaking the ARC treatment at home and in the community will be described. Summary statistics will be used for answers to closed questions and open questions will be thematically analysed.

Objective 8: The views of providers and clinical therapists about delivery of the study treatments will be described. Summary statistics will be used for answers to closed questions and open questions will be thematically analysed.

Objective 9: As this is a pilot study, statistical comparisons of clinical outcomes (e.g. dynamic gait index, see above) and accelerometer data between treatments will not be undertaken and data will be presented as summary descriptive statistics. To determine which outcome measures to take forwards to a main trial, we plan to review data completeness, patient/staff feedback about acceptability and any new emerging literature about most appropriate measures, to inform decisions. This review will also determine the most appropriate primary outcome measure. Data collected for this selected primary outcome measure (e.g. standard deviation) will subsequently be used as appropriate by statisticians to inform a power calculation for a definitive trial.

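### Letting the treating providers collect the participant-views questionnaire creates an avoidable risk of softened answers for Objective 7

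*Protocol article*

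**What the plan says.** Under Participant views of the treatments, each participant receives a questionnaire with closed and open questions. On its return the article states: "The questionnaires will either be collected by the study providers or returned in pre-paid envelopes". It gives no rule for who uses which route and no expected split.

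The two Mode of delivery sections identify the providers. For the intervention: "The ARC intervention treatment will be delivered by two providers (a research physiotherapist and a research associate". For control: "The control treatment will be delivered by two providers (a research physiotherapist and a research associate". The section on providers' own views confirms that the same staff serve both arms: "The therapist/researcher who has provided both the treatments will complete a questionnaire".

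The questionnaire serves Objective 7, listed among the secondary objectives: "To report the views of study participants about undertaking the ARC intervention at home and in the community". The analysis stated for it is descriptive: "Summary statistics will be used for answers to closed questions and open questions will be thematically analysed".

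**The concern.** A participant who found the exercises dull, the metronome irritating or the supervision poor may have to pass that opinion to the person responsible. People in that position are more likely to tone criticism down than to exaggerate it, so any distortion would run towards acceptability. A pilot is run to expose such problems before a definitive trial, and this collection route works against that purpose.

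The two routes also differ in how private they may feel to the participant. As described, the article gives no means of telling afterwards which answers came by which route.

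**Working it through.** The plan states no figure on this point, so there is none to reproduce. The check sets the sections side by side and adds an illustration on assumed values.

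**1. Are the collectors the people who treated the participant?** Yes. The return sentence names the study providers, and the Mode of delivery sections use the same term for the two staff who deliver treatment. In the ARC arm they supervise six of the 18 sessions and give telephone support. In the control arm they make weekly contact, face to face or by telephone.

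**2. Does the article say that providers see the answers?** No. It does not say whether forms are sealed, named, read by the provider or completed in the provider's presence.

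**3. How many forms bear on Objective 7?** Every participant gets a questionnaire, so up to 60 forms exist. Objective 7 as worded covers the ARC intervention only. With 60 participants allocated 1:1, that is 60 / 2 = 30, which agrees with the 30 given under Qualitative analysis.

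**4. What depends on the answers?** The Progression criteria section reads: "Progression criteria have been set based upon recruitment, treatment adherence and data completeness to determine whether progression to a definitive trial is appropriate". Participant views are not among the three criteria. For the choice of outcome measures for the main trial, Data analysis says: "we plan to review data completeness, patient/staff feedback about acceptability and any new emerging literature about most appropriate measures". That feedback concerns outcome measures, and the article does not say that it comes from this questionnaire.

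**5. What other source exists?** Interviews of about one hour with at least five ARC participants who completed the study, continued if saturation is not reached. Five of 30 is 5 / 30 = 17%. The interviews do not cover those who stopped, and the article does not say who conducts them.

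**6. How large could a shift be?** Let f be the share of forms returned through providers and b the inflation of the favourable percentage on that route. The shift in the overall favourable percentage is f × b. The documents give neither value, so both are assumptions.

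| f | b (points) | Shift (points) |
|---|---|---|
| 0 | any | 0 |
| 0.5 | 10 | 5 |
| 1 | 20 | 20 |

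For scale, the 95% half-width for an assumed true 80% favourable with n = 30 is 1.96 × √(0.8 × 0.2 / 30) = 1.96 × 0.073 = 0.143, about 14 points. Over the assumed range (f from 0 to 1, b from 0 to 20 points), the shift runs from nothing to somewhat more than sampling error.

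**The case against.** The strongest reply is that the article says only who may carry the form back. Envelopes and participant instructions are details that a journal article commonly leaves to the full protocol, which is not shown. A pre-paid postal route is open, nothing obliges a participant to use the provider, and the interviews give a second source. The objective is descriptive and no decision to proceed rests on it.

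Most of this stands, and it limits the point. A reader might infer that providers read the forms, or that the answers will be biased. The article supports neither, because it is silent on sealing and on who is present at completion. A reader might also infer that all 60 questionnaires are at stake for Objective 7, or that the progression decision could be distorted. The wording of the objective and the progression criteria rule out both.

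What does not stand is that this is merely an omitted detail. The article positively names the treating providers as one of two collection routes, and that choice can be reviewed as stated. The safeguards are also partial. Post protects only those who use it, and the interviews reach a small group of completers.

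**Conclusion.** The point holds as an avoidable risk in one direction, not as a demonstrated bias. Collection by the treating providers may soften the answers that inform Objective 7, for about 30 ARC participants. The size cannot be derived from the documents. The range of 0 to 20 percentage points rests wholly on assumed values and shows only that the effect could be negligible or could exceed sampling error.

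The conclusion rests on two assumptions: that at least some forms go through providers, and that participants believe the provider could see what they wrote. If the full protocol already requires sealed return to someone outside treatment delivery, the risk is largely met and the sponsor need only confirm it. The objective is secondary and descriptive and sits outside the progression criteria, so this is a cheap improvement and not a defect that threatens the pilot.

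**What to change.** Keep both return routes. Give every participant an envelope addressed to a named role in the study team that neither delivers treatment nor acts as a blinded outcome assessor. The second condition matters because comments about cueing could reveal allocation. Ask participants to seal the form before handing it over or posting it, and tell them that their treating providers will not see their individual answers. That assurance has to be kept through data entry and analysis as well, since one of the providers is a research associate.

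Record the return route and report the number by each route for description only. Do not compare answers by route: no rule assigns the route, so a difference would mix softened answering with who chooses which route, and about 30 forms are too few to support it.

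The cost is envelopes and one sentence in the instructions. Provider collection stays available, so there is no evident reason for response to fall. The Trial status section reports 16 of 60 participants recruited at submission, so if the target is met the change could still have applied to at least 60 − 16 = 44 participants.

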#### Providers’ views of the treatments

The therapist/researcher who has provided both the treatments will complete a questionnaire with a combination of closed and open questions specifically designed for this study in order to ascertain the feasibility of the treatments.

### Qualitative interviews

In order to expand on the findings of the pilot RCT, a qualitative study will also be undertaken. The views of at least five ARC intervention participants will be sought, via interview, alongside the questionnaire data. These interviews will be separate to the main study and undertaken after the 10-week outcome assessments have been completed. Opinions on various aspects of the study will be sought from the first five intervention participants, or until data saturation has been reached.

#### Qualitative analysis

Face-to-face semi-structured interviews of approximately 1 h will be undertaken. From the 30 participants who will have taken part in the ARC treatment programme, an estimated sample of five stroke survivors will be interviewed unless data saturation is reached before this number. Theoretical saturation is defined as being reached when no new themes emerge from the data. If data saturation has not been achieved by this number, further interviews will be conducted. Purposive sampling will be used to recruit participants who were in the ARC intervention group and had completed the study. Purposive sampling has been chosen to ensure a maximum variation sample based on gender, age and stroke-related physical disability.

Potential participants will be invited to take part either by telephone or by email and given a brief description of what the interview might address, such as how they felt about taking part in the study, engagement with the independent training sessions and any impact they perceive on everyday activities. All participants will be asked to provide written informed consent, which will be collected prior to commencing the interview.

Thematic analysis has been chosen to analyse the data as it is a flexible method that allows themes to emerge from the data [41] and has previously been used to analyse data following exercise interventions [42] and physical rehabilitation following stroke [43]. This ‘rigorous thematic approach’ can produce an insightful analysis that answers particular research questions [41]. Thematic analysis is one of the most commonly used methods of analysing qualitative data, as it is simple, less time-consuming and has a flexible approach.

